**In summary:**

*Primary analysis*

1. CVD = #beh + BMI + cova

*Secondary analysis*

1. CVD= #behaviours*BMI group + covariates
2. CVD= individual behaviours*BMI group + covariates

*Supplementary analysis*

1. CVD=#behaviours*BMI group*Metabolic Conditions + covariates

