## **Exposures**

Four healthy behaviours will be classed as exposures all measured at cohort inception from a questionnaire administered then. These will be analysed separately and then as a total number of healthy behaviours. No data to estimate change in these variables is available:

1. *Smoking status.* This will be classified as “Never”, “Current” and “Previous” as per smoking status self-reported by the UK Biobank participants. Being a never smoker is defined as a healthy behaviour.
2. *Alcohol intake frequency*. To be divided into “None”, “Occasional” (<1 unit/ week), “Moderate” (1-14 units/ week) and “Heavy” (>14 units/ week). A healthy behaviour for this study is defined as ‘none’ or ‘occasional’ alcohol intake. Data was calculated from participants’ responses to estimate consumption of red wine^†^; champagne and white wine ^†^; beer and cider^†^; spirits^†^; fortified wine^†^.
3. *Fruit and Vegetable Score.* The sum of the following variables was calculated: Fresh fruit intake^†^, raw vegetable intake^†^, cooked vegetable intake. These were summed and a healthy behaviour defined as 5 or more servings of fruit and vegetables a day.
4. *Physical Activity.* Derived MET score from number of days/week of vigorous physical activity 10+ minutes^†^; Duration of vigorous activity; number of days/week of moderate physical activity 10+ minutes^†^; duration of moderate activity and number of days/week walked 10+ minutes^†^; duration of walks ^†.^ A healthy behaviour was defined as 150 or more minutes of moderate activity, or 75 minutes or more of vigorous activity a week, or a combination of the two, as defined by the UK CMO physical activity guidelines.

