## 2. Plan for dealing with missing data

- Participants with missing data in key variables will be dropped:
  - If the exposure measurements smoking status, alcohol intake, fruit and vegetable score, physical activity score were missing or unknown.
  - Other key confounders in the model: Townsend score, education, age, sex, region of UK, family history of diabetes or hypertension, if missing, we will create a category called “Unknown”
  - If menopausal status is missing, age >=55 will be used as a proxy.
  - If key stratification variable BMI was missing or unknown.

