### For both the primary and secondary analysis:

1. Timescale for the Cox model:

Time from inception to incident of disease will be represented by age. We will use the following command in Stata before the model: stset age_out, id(ID) fail(outcome) enter(age_in)

1. Adjustment:

We will use a multivariable confounding model adjusted for: Age, Townsend score, education, sex, region of UK, family history of diabetes or hypertension and menopausal status.

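### The individual-behaviour models do not state adjustment for the other three behaviours, which leaves each hazard ratio open to confounding, by smoking above all

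*SAP*

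**What the plan says.** The Exposures section gives the four behaviours one role: "Four healthy behaviours will be classed as exposures all measured at cohort inception". They are smoking, alcohol, fruit and vegetable intake, and physical activity. It then says: "These will be analysed separately and then as a total number of healthy behaviours".

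The closing summary lists two secondary models. The first uses the number of behaviours by BMI group. The second is "CVD= individual behaviours*BMI group + covariates".

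The adjustment set appears once, under a heading that begins "For both the primary and secondary analysis". The model is to be "adjusted for: Age, Townsend score, education, sex, region of UK, family history of diabetes or hypertension and menopausal status". The covariate coding list under Covariates & Effect Modifiers adds ethnicity but no behaviour.

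The missing-data section drops participants under this condition: "If the exposure measurements smoking status, alcohol intake, fruit and vegetable score, physical activity score were missing or unknown". Everyone analysed therefore has all four behaviours recorded.

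**The concern.** A count of behaviours gives each behaviour the same weight, so it cannot show which one matters in which BMI group. Only the second secondary model can. If that model takes one behaviour at a time with the stated covariates, the hazard ratio for alcohol, diet or activity absorbs part of the smoking effect wherever smoking differs between the levels of that behaviour. The same applies among the other behaviours, and to the smoking hazard ratio itself.

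Two things are at stake. A behaviour with little effect of its own could appear harmful or protective. And if smoking differs across the levels of a behaviour by different amounts in different BMI groups, the interaction with BMI, which is the purpose of the model, is distorted as well.

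Nothing else in the plan addresses this. Townsend score and education stand in for smoking only in part, and the single sensitivity analysis, which discards early follow-up, is aimed at reverse causality.

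**Working it through.** **Reading the text.** The SAP gives no hazard ratio, event count or smoking prevalence, so there is no figure of its own to reproduce. The first check sets the sections side by side.

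| Item | Smoking, alcohol, diet or activity included? |
|---|---|
| Adjustment set for the primary and secondary analyses | None |
| Covariate coding list | None |
| Summary, secondary model 2 | As exposures; whether singly or jointly is not stated |
| Any statement of mutual adjustment | None found |

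The summary files the individual-behaviour model under the secondary analysis, so the stated adjustment set applies to it on its face.

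**Scale.** All inputs from here on are assumptions; none comes from the SAP. Suppose a behaviour has no effect of its own. With p_u and p_h the smoking prevalence at its unhealthy and healthy levels, and HR_s the smoking hazard ratio, the apparent hazard ratio is approximately

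B = [1 + p_u(HR_s − 1)] / [1 + p_h(HR_s − 1)].

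| p_u vs p_h | HR_s = 1.5 | HR_s = 2.0 | HR_s = 2.5 |
|---|---|---|---|
| 10% vs 10% | 1.00 | 1.00 | 1.00 |
| 15% vs 10% | 1.075/1.050 = 1.02 | 1.150/1.100 = 1.05 | 1.225/1.150 = 1.07 |
| 20% vs 8% | 1.100/1.040 = 1.06 | 1.200/1.080 = 1.11 | 1.300/1.120 = 1.16 |
| 50% vs 40% (ever smoking) | 1.250/1.200 = 1.04 | 1.500/1.400 = 1.07 | 1.750/1.600 = 1.09 |
| 55% vs 30% (ever smoking) | 1.275/1.150 = 1.11 | 1.550/1.300 = 1.19 | 1.825/1.450 = 1.26 |

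With current and former smoking kept apart, each bracket becomes 1 + p_c(HR_c − 1) + p_f(HR_f − 1).

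- Small gaps and low hazard ratios: current 12% vs 8%, former 35% vs 30%, HR_c 2.0, HR_f 1.2. B = (1 + 0.12 + 0.07)/(1 + 0.08 + 0.06) = 1.19/1.14 = 1.04.
- Wide gaps and high hazard ratios: current 20% vs 7%, former 45% vs 22%, HR_c 3.0, HR_f 1.3. B = (1 + 0.40 + 0.135)/(1 + 0.14 + 0.066) = 1.535/1.206 = 1.27.

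**Direction.** If the gap is reversed, the factor falls below 1. At 10% unhealthy vs 15% healthy with HR_s = 2.0, B = 1.10/1.15 = 0.96.

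**Interaction.** If the gap were 15% vs 10% in one BMI group and 20% vs 8% in another, both with HR_s = 2.0, the ratio of the two hazard ratios would be off by (1.200/1.080)/(1.150/1.100) = 1.06 through smoking alone.

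The formula ignores the stated covariates. Only the smoking gap that remains after adjustment for age, deprivation, education, sex and region would bias the result.

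**The case against.** The strongest reply is that the plan is silent rather than wrong. The summary writes a single equation with a plural term, which could mean four separate terms in one model, and that is mutual adjustment. The Exposures wording may only contrast the components with their sum. The adjustment list is also not exhaustive: the summary's primary model contains BMI, which the list omits. The text on the secondary analysis describes only the number of behaviours, for which leaving the components out of the covariates is correct.

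This ambiguity is real, so it cannot be said with certainty that the models will be unadjusted. It does not remove the point. The more natural reading is one behaviour at a time, no section states joint entry, and the two readings give different hazard ratios.

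A reader might go further and infer that the alcohol, diet and activity hazard ratios are confounded by smoking, are biased upward, and will shrink once adjusted. The SAP does not support that, because it gives no smoking prevalence by behaviour. For alcohol, the healthy level is no intake or less than 1 unit a week, so people drinking 1–14 units count as unhealthy. Whether smoking is more common on that side of the split cannot be told from the document. Apart from the equal-prevalence row and the reversed example, every illustration above assumes more smoking in the unhealthy group, so a factor above 1 is built in. The 1.27 needs the widest gaps and the highest hazard ratios together.

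**Conclusion.** The point stands in limited form. As most naturally read, the individual-behaviour models adjust for none of the other three behaviours, so each hazard ratio is open to confounding by them, with smoking the main worry. This is more than a missing detail, because the SAP does state an adjustment set and that set omits measured risk factors.

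The size is unknown. The illustrative factor runs from 1.00 with equal smoking prevalence to about 1.27, before covariate adjustment, and could be below 1. It rests on assumed prevalences and smoking hazard ratios.

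It would be wrong to infer that the main results are undermined. Smoking is part of the count, so the primary analysis and the analysis of the count by BMI group are not affected in this way. The change should be made, but it concerns one secondary model.

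**What to change.** In the Adjustment item and in the summary's second secondary model, state that every individual-behaviour model also includes the other three behaviours. When they serve as adjusters, smoking should enter as never, previous or current and alcohol in the four levels that the Exposures section already defines. A never/ever split would pool current with former smokers and leave residual confounding.

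Whether the BMI interaction is then added for one behaviour at a time or for all four together is a matter of preference. Either is acceptable if it is stated.

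The cost is one sentence and a few more terms. Smoking in three levels adds 2, alcohol in four adds 3, and diet and activity as yes/no add 1 each. That is 2 + 3 + 1 = 6 extra terms in the diet or activity model, 3 + 1 + 1 = 5 in the smoking model, and 2 + 1 + 1 = 4 in the alcohol model. No new data are needed and no participants are lost, because anyone missing a behaviour is already excluded.
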